### Sample Size

The sample size will be 30 patients. As referenced in the literature, when the SD and population frequencies of a given variable are not known, a pretest should be performed with 30 to 40 patients, and data from this group should be considered a population estimate [24]. After collecting blood glucose data for the first and third weeks, the mean glycemic variability and the SD will be calculated so that the sample size can be recalculated. This is necessary because there are no similar studies in the literature. If the recalculated sample size is less than 30, no new participants will be needed and the study will be concluded. If the new sample size is greater than 30, new patients will be recruited until the new, larger sample size is reached.

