**Methods:**

This study will use a crossover, randomized, double-blind, placebo-controlled trial design. Patients with T2DM in group 1 will receive 3 mg of melatonin at 9:00 PM in the first week, undergo a washout period in the second week, and receive a placebo in the third week (melatonin-washout-placebo). Group 2 will be randomized to receive a placebo-washout-melatonin sequence (3 mg). Capillary blood glucose levels will be measured at 6 different times before and after meals during the last 3 days of the first and third weeks. The study aims to compare the mean differences in blood glucose levels and the coefficient of glycemic variability in patients receiving melatonin and placebo during the first and third weeks. After analyzing the initial results, the number of needed patients will be recalculated. If the recalculated number is higher than 30, new participants will be recruited. Thirty patients with T2DM will be randomized into the 2 groups: melatonin-washout-placebo or placebo-washout-melatonin.

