### Statistical Analysis

If quantitative variables adhere to a normal distribution, as represented by the Gaussian curve, their central tendency will be expressed as mean and their dispersion will be quantified by the SD. If the distribution of these variables does not follow a normal distribution, then their central tendency will be described by the median and their dispersion will be characterized by the 25% and 75% quartiles. The Shapiro-Wilk test will be used to assess normality. Categorical variables will be presented using both absolute frequencies and percentages.

Statistical analyses of normal quantitative variables, both before and after the intervention, will be conducted using a paired 1-tailed *t* test. When the distribution is not normal, the Wilcoxon test will be used. The study will have 2 intervention tails: placebo-washout-melatonin and melatonin-washout-placebo. Comparison of blood glucose levels will be performed between the time when the patients used melatonin and the time they used placebo.

The patients will be compared with one another based on the capillary blood glucose results obtained during the first and third weeks.

The epidemiological, clinical, and laboratory data of the patients will be compared between groups 1 and 2 in order to evaluate whether the randomization process has generated groups that lack statistical differences that may influence the research results.

The significance level will be .05 and the software of choice will be SPSS (version 20.0; IBM Corp).

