## Results

Participant recruitment took place between March 2023 to April 2023. In all, 30 participants were eligible and completed the study. Upon selection of these patients and completion of the 3-week research period, a statistical analysis was conducted on the variability of capillary blood glucose levels during the first and third weeks. Subsequently, these data were used to determine the required sample size (n) necessary to draw valid conclusions regarding the proposed research objectives. Furthermore, in addition to the capillary blood glucose values, the data types presented in Table 1 will be scrutinized to ensure the absence of statistical discrepancies between groups 1 and 2. The study was approved by the Brazilian Registry of Clinical Trials (RBR-6wg54rb) on March 7, 2023. Figure 2 shows a sample table of how the results will be presented.

**Table 1 table1:** Epidemiological, clinical, and laboratory data (n=30).

Characteristics	Values
Participants	n
Age (years)	Mean or median
Sex (female)	n, %
Insulin users	n, %
BMI (kg/m^2^)	Mean or median
Abdominal circumference (cm)	Mean or median
Duration of diabetes (years)	Mean or median
STOP-Bang^a^ (score)	Mean or median
Glycohemoglobin (%)	Mean or median

^a^STOP-Bang: snoring, tiredness, observed apnea, high blood pressure, BMI, age, neck circumference, gender.

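### The sample size is recalculated from the first 30 patients' outcome with no fixed target difference or maximum n, those patients are kept, and the final test is an unadjusted one-tailed .05

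*Protocol article*

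**What the plan says.** All references are to the protocol article.

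- **Sample Size** sets the first stage: "The sample size will be 30 patients". The figure comes from a pretest convention under which "a pretest should be performed with 30 to 40 patients, and data from this group should be considered a population estimate".
- The same section says that after both treatment weeks "the mean glycemic variability and the SD will be calculated so that the sample size can be recalculated". If the recalculated number is below 30, the study ends. If not: "If the new sample size is greater than 30, new patients will be recruited until the new, larger sample size is reached". The first 30 therefore count toward the final number.
- **Abstract, Methods** gives the order of events: "After analyzing the initial results, the number of needed patients will be recalculated".
- **Results** reports that this has happened. For the first 30, "a statistical analysis was conducted on the variability of capillary blood glucose levels during the first and third weeks", and then: "Subsequently, these data were used to determine the required sample size (n) necessary to draw valid conclusions regarding the proposed research objectives".
- **Statistical Analysis** specifies a one-tailed paired t test, or a Wilcoxon test if the data are not normal, and says "The significance level will be .05".

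The article states no target difference, power, maximum sample size, adjustment for the interim decision or method of combining the two stages.

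**The concern.** A sample size formula for a paired comparison needs a difference and an SD. The article names a mean and an SD, both from the first 30 patients, treats those data as the population value, and offers no difference from elsewhere. Followed as written, the rule most naturally inserts the observed effect.

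The decision to stop or extend then depends on the result, and an ordinary test of the pooled data ignores that dependence. Three things are at stake for the primary endpoint: the one-sided 5% error rate, the size of the reported effect if the study ends at 30, and control over how large the study becomes.

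**Working it through.** **Inputs from the article:** first stage 30 patients; stop if recalculated n is below 30, otherwise recruit to n with the 30 retained; one-tailed paired t test at .05; no maximum n.

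**Assumptions:** 80% power (90% as a variant), normally distributed within-patient differences, and various caps and true effects, since the article gives none of these.

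**The plan's own figure.** The 30 cannot be reproduced, because no effect, SD or power accompanies it. A fixed-n paired t test with 30 patients simulates at 5.0%, so the nominal level is sound without the recalculation.

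**Recalculation on the natural reading.** With d the observed mean difference divided by its SD,

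n = ((1.645 + 0.842) / d)² ≈ 6.18 / d².

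- Stopping at 30 requires d ≥ √(6.18/30) = 0.454.
- d = 0.4 gives 39; d = 0.2 gives 155; d = 0.1 gives 619; d = 0.05 gives about 2,470. As d approaches zero, n has no limit.
- With a true effect of 0.4, which needs 39 patients, the realised n runs from 30 to about 560 (5th to 95th percentile).

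**Type I error** (no true effect, pooled one-sided .05 test, 400,000 simulated trials; repeat runs differ by about 0.1 point):

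| Cap on n | Extend whatever the direction | Stop if the direction is wrong |
|---|---|---|
| 40 | 5.2% | 5.3% |
| 60 | 5.9% | 5.8% |
| 120 | 6.8% | 6.2% |
| none | 7.7% | 6.4% |

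A normal-theory integral gives 5.7% at a cap of 60 and 7.5% uncapped. At 90% power, the range when extending whatever the direction is 5.1% (cap 40) to 7.0% (uncapped).

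**Estimate at a favourable stop.** The stopping boundary corresponds to a test statistic of 0.454 × √30 = 2.49, above the critical value of 1.70 on 29 degrees of freedom. Every favourable stop is therefore already significant. In units of the true SD:

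| True effect | Trials stopping favourably at 30 | Mean estimate among them |
|---|---|---|
| 0.2 | about 10% | 0.51 |
| 0.3 | about 22% | 0.54 |
| 0.4 | about 40% | 0.57 |
| 0.5 | about 60% | 0.61 |

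**Alternative reading.** If only the SD is updated and the difference is preset (0.25 to 0.5 SD assumed), type I error is 5.1% to 5.4%. The stop then no longer depends on the observed mean, so the exaggeration disappears.

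**The case against.** The strongest reply is that the mechanism is inferred. No formula is given, the mean named could be the level of variability rather than the treatment difference, and the pretest is justified by an unknown SD, which is a nuisance parameter. This stands as far as certainty goes. But an SD-only recalculation needs a preset difference; the article states none and says that no similar studies exist.

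A second reply is that such detail belongs in an analysis plan or full protocol. That covers the exact formula. It does not cover a stop-or-extend rule, its inputs and a .05 level that the article itself fixes.

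A third is that blinding protects. Under Blinding, only the identity of bottles 1 and 2 is hidden. The size of the difference between them is visible, and that is enough to drive n.

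A fourth is that the inflation is modest. It is, and it arises mainly from extension: with no true effect, only about 1% of trials stop favourably at 30.

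Some stronger readings are tempting but not supported:

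- A reader might infer that significance at 30 also counts as success, which would give 8.0% to 9.8%. The rule ends the study only when the recalculated n is below 30.
- A reader might infer that the between-patient SD is used in place of the SD of within-patient differences. The article does not say which SD it means, and it specifies a paired test.
- A reader might infer that the trial was extended. The article reports 30 completers and a recalculation, and does not show what followed.

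**Conclusion.** The concern holds in a limited form. The article fixes an outcome-informed stop-or-extend rule without a target difference, a maximum n or error control. If the observed effect drives n, which is a strong inference and not stated text, the one-sided error is about 5.2% to 7.7% at an assumed 80% power, or 5.3% to 6.4% if a wrong-direction result ends the trial.

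The larger harms are the exaggerated estimate at a favourable stop, more than 2.5 times the truth when the truth is 0.2 (0.51 / 0.2 = 2.55), and a sample size with no upper limit. A reader might conclude that the stated error rate certainly fails. The documents do not support that, because under an SD-only recalculation with a preset difference it holds approximately.

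**What to change.** State the target difference in the primary variability measure, chosen on clinical grounds and not from the first 30 patients' data, together with the power and a maximum n. Recalculate only from the SD of the within-patient differences. If that was always the intention, adding these statements settles the point.

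If the difference at 30 was already used, disclose it. What follows depends on the decision taken:

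- **Patients are added:** do not use the pooled test at .05. Combine the first-30 and later-patient results with a combination test, such as the inverse-normal, whose weights are fixed before any later data are seen. State a stage-1 boundary so that a stop at 30 falls within the overall .05. Because the first-30 analysis has been run, use conventional weights that do not depend on its result, and say when they were chosen.
- **The study stopped at 30 under the rule:** report that the estimate is conditional on the rule and likely too large.

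The cost is an amended sample size section, the work of justifying a target difference, a slightly more involved final test and a small loss of efficiency.

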### Statistical Analysis

If quantitative variables adhere to a normal distribution, as represented by the Gaussian curve, their central tendency will be expressed as mean and their dispersion will be quantified by the SD. If the distribution of these variables does not follow a normal distribution, then their central tendency will be described by the median and their dispersion will be characterized by the 25% and 75% quartiles. The Shapiro-Wilk test will be used to assess normality. Categorical variables will be presented using both absolute frequencies and percentages.

Statistical analyses of normal quantitative variables, both before and after the intervention, will be conducted using a paired 1-tailed *t* test. When the distribution is not normal, the Wilcoxon test will be used. The study will have 2 intervention tails: placebo-washout-melatonin and melatonin-washout-placebo. Comparison of blood glucose levels will be performed between the time when the patients used melatonin and the time they used placebo.

The patients will be compared with one another based on the capillary blood glucose results obtained during the first and third weeks.

The epidemiological, clinical, and laboratory data of the patients will be compared between groups 1 and 2 in order to evaluate whether the randomization process has generated groups that lack statistical differences that may influence the research results.

The significance level will be .05 and the software of choice will be SPSS (version 20.0; IBM Corp).

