### Randomization

Patients will be randomized into two groups. Group 1 will use the substance contained in bottle 1 in the first week, will not use any substance in the second week (the washout period), and will use the substance contained in bottle 2 in the third week. Group 2 will use the substance contained in bottle 2 in the first week, will not use any substance in the second week (the washout period), and will use the substance contained in bottle 1 in the third week.

Patients will be divided into these groups according to the result of rolling a die. Those who roll a number from 1 to 3 will be in group 1, while those who roll a number from 4 to 6 will be in group 2. When the number of participants in a group reaches 15, patients will be automatically allocated to the other group until it includes 15 participants. The project researcher will know which patients will use bottle 1 or 2 in the first and third weeks but will not know which bottle contains placebo and which contains melatonin.

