### Procedures

Patients with T2DM will be selected to take part in this study during routine consultations held in an outpatient endocrinology clinic. At the end of the consultation, the endocrinologist, when verifying that the patient meets the inclusion criteria, will ask the patient if they are interested in participating in research on diabetes and melatonin. This question will be followed by reading the informed consent form. All stages of the research will be explained to the patient. This includes the research period, the use of a placebo substance and melatonin, the need to perform capillary blood glucose measurement 6 times a day for 3 days in the first week and 3 days in the third week, the washout period, and the delivery of capillary blood glucose results after the 3 weeks of the project. If the patient agrees to participate in the project, the researcher will ask them to sign the free and informed consent form. A copy of this form will be given to the patient. Next, the researcher will ask the patient to roll a die. Patients who roll a number from 1 to 3 will be in group 1 and will be included in the group that uses the following sequence: bottle 1, washout, bottle 2. Those who roll a number from 4 to 6 will be included in group that uses the following sequence: bottle 2, washout, bottle 1. After allocating the patient to one of the groups, the project researcher will fill in the research record, which will contain the epidemiological, clinical, and laboratory data of the patient, including age, gender, duration of diabetes, history of epilepsy, insulin use (or not), STOP-Bang (snoring, tiredness, observed apnea, high blood pressure, BMI, age, neck circumference, and gender) questionnaire results, weight, height, BMI, abdominal circumference, and glycohemoglobin value. After this step, the patient will be guided on the diet and physical activity regimens to be carried out during the 3 weeks of the project. Patients will be instructed to perform 30 minutes of physical activity 5 times a week during the 3 weeks of the project. After this guidance, patients will receive a glucometer, strips for measuring capillary blood glucose, and lancets to take home. In addition, patients will be given a form to record capillary blood glucose values. At the end of the third week, the patient will return with the blood glucose values.

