### Limitations

The limitations inherent in this study pertain to an analysis of glycemic variability conducted over a short span: only a few days after intake of melatonin or placebo. The effectiveness of melatonin in reducing glycemic variability might occur with longer use.

A second limitation of this study is derived from the fact that endogenous melatonin peaks in the middle of the night. The exogenous melatonin administered to patients in this study will not reproduce the physiological rhythm of endogenous melatonin.

A third limitation is the fact that patients may have diet and physical activity fluctuations between weeks 1 and 3 of the study, despite the guidance given initially, which might interfere with glycemic variability.

A fourth limitation of this study is the fact that we will not assess the prevalence of the *MTNR1B* mutation, which can determine a poorer glycemic response to melatonin use.

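### The pooled paired test leaves period out of a two-sequence crossover: a common week 1 to week 3 shift would cost power and inflate the SD, and would bias the estimate only if the sequences are unequal

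*Protocol article*

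**What the plan says.** The Statistical Analysis section of the protocol article fixes the test. "Statistical analyses of normal quantitative variables, both before and after the intervention" "will be conducted using a paired 1-tailed *t* test", and "When the distribution is not normal, the Wilcoxon test will be used". The contrast is then named: "Comparison of blood glucose levels will be performed between the time when the patients used melatonin and the time they used placebo". On alpha: "The significance level will be .05". Neither this section nor any other mentions a period or sequence term. The section on carryover argues only that one week of washout is enough.

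On conditions that could differ between the two measured weeks, Procedures has the regimen start at enrolment, after allocation: "Patients will be instructed to perform 30 minutes of physical activity 5 times a week during the 3 weeks of the project". No run-in is described. Limitations concedes that "patients may have diet and physical activity fluctuations between weeks 1 and 3 of the study" and offers no analytic remedy.

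On balance, Randomization states: "When the number of participants in a group reaches 15, patients will be automatically allocated to the other group until it includes 15 participants". The Sample Size section allows recruitment beyond 30 after a recalculation based on the first patients' mean and SD. The article gives no rule for balancing the sequences among added patients.

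**The concern.** A before-and-after paired test suits a single group measured twice. Here half the patients take melatonin in week 1 and half in week 3. If glycemic variability shifts between those weeks for everyone, whatever the treatment, the melatonin-minus-placebo difference moves one way in one sequence and the opposite way in the other. The pooled test counts that separation as random error. Washout does not help: a period effect can exist with no carryover at all.

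Three things are at stake. The test loses power that the crossover design has already provided. The SD that may drive the sample size recalculation is too large, so a period effect alone could trigger an extension. And if the analysed sequences are unequal, part of the shift enters the treatment estimate.

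**Working it through.** **Inputs.** From the article: a paired one-tailed t test, alpha 0.05, N = 30, and 15 patients per sequence forced by the cap. Not in the article: an effect size, an SD, a target power, or the size of any week 1 to week 3 shift. The 30 is a pretest size taken from a general reference, so no power formula can reproduce it. As an anchor, a paired one-sided t test with N = 30 has 80% power at a true difference of 0.465 SD (noncentral t). The shift is assumed to be 0, 0.25, 0.5 or 1.0 SD.

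**Model.** Let d be a patient's benefit of melatonin over placebo, with SD 1 within each sequence and mean τ. Let π be the week 3 minus week 1 shift on the benefit scale (positive means improvement by week 3). Then

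- melatonin first: E(d) = τ − π
- placebo first: E(d) = τ + π

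For the pooled paired estimate, with n₁ melatonin-first and n₂ placebo-first patients and N = n₁ + n₂:

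- bias = π(n₂ − n₁)/N
- expected sample variance of d = 1 + 4π²n₁n₂/[N(N − 1)]

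**At 15/15.** Bias = π × 0/30 = 0. The variance is 1 + 4π² × 225/(30 × 29) = 1 + 1.034π². Power and type I error are from simulation at τ = 0.465 and τ = 0.

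| π (SD) | Variance | SD of d | Power, paired | Power, period-adjusted | One-sided type I error, paired |
|---|---|---|---|---|---|
| 0 | 1.000 | 1.00 | 80% | 80% | 5% |
| 0.25 | 1.065 | 1.03 | 78.5% | 80% | about 4.5% |
| 0.5 | 1.259 | 1.12 | 74% | 80% | about 3.3% |
| 1.0 | 2.034 | 1.43 | 55% | 80% | about 1% |

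The adjusted analysis keeps its type I error at about 5% throughout.

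**Recalculated sample size.** Required N scales roughly with the variance: 30 × 1.065 = 31.9, 30 × 1.259 = 37.8 and 30 × 2.034 = 61.0. Solving with the noncentral t gives 32, 38 and 60. This applies only if the SD used is that of the pooled paired differences; the article does not say which SD is meant.

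**Unequal sequences.** Take an extension to 60 that ends at 25 melatonin-first and 35 placebo-first, with π = 0.5. Bias = 0.5 × 10/60 = +0.083 SD in favour of melatonin, and the one-sided type I error is about 11.5%. In the mirror split, 35/25, bias is −0.083 SD and the type I error is about 0.7%. If the 30 added patients were allocated by die alone (an assumption), a split of 20:10 or worse in one given direction has probability 4.9%. A sequence difference of at least 4 in either direction has probability 58%. Averaged over such fair allocation the bias is zero, and the paired test's type I error is about 4.7%, 4% and 3% at shifts of 0.25, 0.5 and 1.0 SD, which is below nominal.

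**The case against.** The strongest reply is that the first 30 patients all completed. The cap makes them 15/15, so in the cohort at hand the paired estimate is unbiased and the test errs on the safe side. That stands. A reader might infer from the unequal-split figures that the plan inflates the false-positive rate. The documents do not support this: inflation is conditional on an unlucky split in one direction, the mirror split does the opposite, and the average over fair allocation is below 5%. How added patients would be balanced may also be set out in a fuller document.

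A second reply is that a common trend is not established. Limitations says only that individual patients may vary, which is partly ordinary within-patient noise that no period term removes. That the regimen is new to patients is an inference, since prior habits are not stated. Measurement begins on day 5, so the first days under the guidance are not measured. This also stands: a trend is plausible, not to be expected, and at 0.25 SD the power loss is under 2 points.

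Neither reply is a reason to leave period out, since including it costs almost nothing when there is no trend.

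The Figure 2 caption mentions unpaired t tests, and a reader might take that to mean a between-sequence comparison of period differences. The caption states no period adjustment and conflicts with the Statistical Analysis section, so it cannot be relied on for this.

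**Conclusion.** The point holds as one of efficiency and of the recalculation. The article fixes a pooled paired test that ignores period, in a design where a common shift between the two measured weeks is plausible. At 15/15 the estimate is unbiased. For assumed shifts of 0.25, 0.5 and 1.0 SD, power falls from 80% to about 78.5%, 74% and 55%, the test becomes conservative, and a required N of 30 could be read as about 32, 38 or 60. The 80% anchor and the shift sizes are assumptions; with no shift there is no loss. Bias arises only if the sequences in the analysed data are unequal, for instance after an extension, and its direction follows the imbalance. The change should be made, but the paired result in the first 30 patients is not invalid.

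**What to change.** Analyse by the randomised sequence. For each patient take week 1 minus week 3, compare the two sequences with a two-sample t test, and halve the difference in means to estimate the treatment effect. At 15/15 its standard error is ½ × s × √(1/15 + 1/15) = s/√30, with s the pooled within-sequence SD and 28 degrees of freedom instead of 29. A mixed model with treatment, period and sequence and a random patient effect is an alternative. If the data are not normal, use the rank-sum test on the period differences between sequences. Base the sample size recalculation on the within-sequence (period-adjusted) SD, and show results by sequence. If recruitment goes beyond 30, state how the sequences will be kept balanced.

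The statistical cost is one degree of freedom and no new data. There is a procedural cost: Results reports that the first 30 patients' data have already been analysed for variability. The change should therefore be dated and disclosed, with the stated paired test reported as a sensitivity analysis.
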